##### *4.5.3.2 MEWS score*

Modified early warning system score (MEWS) will be assessed at Day 1 and Day 15 and recorded in the CRF if ICU is needed.

##### *4.5.3.3 SpO2*

Resting peripheral capillary oxygen saturation (SpO2) will be measured 3 times per day by pulse oxymetry at Visits 1 to 4 and recorded in the CRF. Saturation normalization will be measured, both as an absolute value and as a relative value with respect to the baseline situation of income.

#### 4.5.3.4 Oxygen supplementation

Oxygen supplementation will be assessed at Visits 1 to 5. The date, time and amount of supplementation will be recorded in the CRF.

#### 4.5.3.5 Thorax radiography

A thorax radiography (Rx) will be performed at screening and Visit 4 (Day 15). The Rx scan will be recorded in the CRF and reported as “normal” or “abnormal”.

Any abnormalities reported at screening should be specified and recorded as medical history.

#### 4.5.3.6 Laboratory assessments

Blood samples for determination of the laboratory assessments described in Table 4 will be drawn at Visits 1 to 4. The date and time of blood sampling will be recorded in the CRF.

Table 4 Laboratory assessments:

|                                                                                          |                                            |
|------------------------------------------------------------------------------------------|--------------------------------------------|
| Biochemistry                                                               | Hematology                   |
| Aspartate aminotransferase (AST)                                                         | Hemoglobin                                 |
| Alanine aminotransferase (ALT)                                                           | ESR                                        |
| Total bilirubin (if >upper limit of normal also conjugated and non-conjugated bilirubin) | Platelet count                             |
| Prothrombin Time/International Normalized Ratio (PT-INR)                                 | White blood cells                          |
| Fibrinogen                                                                               | RBC                                        |
| Cardiac troponin                                                                         | Differential blood count                   |
| Creatinine                                                                               | Hyperinflammatory parameters |
| C-reactive protein (CRP)                                                                 | Ferritin                                   |
|                                                                                          | LDH                                        |
|                                                                                          | D-dimers                                   |
|                                                                                          | IL-6                                       |

All laboratory samples will be analyzed at the respective local hospital laboratory according to their standard routines.

#### 4.5.3.7 Survival and hospital discharge

Data on survival and hospital discharge will be collected at Visits 5 and 6 and recorded in the CRF.

#### 4.5.4 Safety assessments

##### 4.5.4.1 *Adverse events*

###### Adverse event (AE)

The safety profile of anakinra has been consistent across indications, age groups, and doses studied; this includes data that have been reported in the literature for off-label indications. The safety profile has remained stable also when anakinra has been studied in long-term safety studies and in patients with various co-morbidities. There are no indications of increasing AE rates over time. The most common AEs are non-serious, mostly mild to moderate injection site reaction that usually occur early and resolve during continued anakinra treatment.

An AE is any adverse change, i.e., any unfavorable and unintended sign, including an abnormal laboratory finding, symptom, or disease that occurs in a patient during the course of the study, whether or not considered by the investigator as related to study treatment.

All AEs for the patients that have received anakinra should be reported irrespective of causality to meet regulatory requirements. The sponsor of the study is responsible for expedited reporting as per regulatory requirement.

A treatment-emergent AE is any AE temporally associated with the use of study treatment whether or not considered by the investigator as related to study treatment.

Adverse events include:

- Exacerbation of a pre-existing disease.
- Increase in frequency or intensity of a pre-existing episodic disease or medical condition.
- Disease or medical condition detected or diagnosed during the course of the study even though it may have been present prior to the start of the study.
- Continuous persistent disease or symptoms present at study start that worsen following the start of the study (i.e., signing of informed consent).
- Abnormal assessments, e.g., change on physical examination, ECG findings, if they represent a clinically significant finding that was not present at study start or worsened during the course of the study.

- Laboratory test abnormalities are considered as AEs if they represent a clinically significant finding, symptomatic or not, which was not present at study start or worsened during the course of the study or led to dose reduction, interruption or permanent discontinuation of study treatment. An AE is any untoward medical occurrence in a patient administered a pharmaceutical product; the event does not necessarily have a causal relationship with the treatment or usage.

#### Intensity of adverse events

The intensity of clinical AEs is graded on a three-point scale – mild, moderate, severe – and is reported on specific AE pages of the CRF.

If the intensity of an AE worsens during study treatment administration, only the worst intensity should be reported on the AE page. If the AE lessens in intensity, no change in the severity is required.

If the intensity of an AE with an onset date between informed consent signature and start of study treatment and which is ongoing at the start of treatment worsens after the start of study treatment, a new AE page must be completed. The onset date of this new AE corresponds to the date of worsening in intensity.

The three categories of intensity are defined as follows:

- Mild: The event may be noticeable to the patient. It does not influence daily activities, and usually does not require intervention.
- Moderate: The event may make the patient uncomfortable. Performance of daily activities may be influenced, and intervention may be needed.
- Severe: The event may cause noticeable discomfort, and usually interferes with daily activities. The patient may not be able to continue in the study, and treatment or intervention is usually needed.

A mild, moderate, or severe AE may or may not be serious, see Section 5.5.4.2. These terms are used to describe the intensity of a specific event. Medical judgment should be used on a case-by- case basis.

Seriousness, rather than severity assessment, determines the regulatory reporting obligations.

---

### Relationship to study treatment

Each AE must be assessed by the investigator as to whether or not there is a reasonable possibility of causal relationship to the study treatment and reported as either related or unrelated. The determination of the likelihood that the study treatment caused the AE will be provided by an investigator who is a qualified physician.

#### *4.5.4.2 Serious adverse events*

### Definitions of serious adverse events

An SAE is defined by the International Conference on Harmonisation (ICH) guidelines as any AE fulfilling at least one of the following criteria:

- Fatal.
- Life-threatening: refers to an event in which the patient was at risk of death at the time of the event. It does not refer to an event that hypothetically might have caused death had it been more severe.
- Requiring inpatient hospitalization, or prolongation of existing hospitalization.
- Resulting in persistent or significant disability or incapacity.
- Congenital anomaly or birth defect.
- Medically significant: refers to important medical events that may not immediately result in death, be life-threatening, or require hospitalization but may be considered to be SAEs when, based upon appropriate medical judgment, they may jeopardize the patient, and may require medical or surgical intervention to prevent one of the outcomes listed in the definitions above.

The following reasons for hospitalization are exempted from being reported:

- Hospitalization for cosmetic elective surgery, or social and/or convenience reasons.
- Hospitalization for pre-planned (i.e., planned prior to signing informed consent) surgery or standard monitoring of a pre-existing disease or medical condition that did not worsen, e.g., hospitalization for coronary angiography in a patient with stable angina pectoris.

However, complications that occur during hospitalization are AEs or SAEs (for example if a complication prolongs hospitalization).

---

#### 4.5.4.3 Reporting requirement of adverse events

##### Reporting of adverse events

Irrespective of seriousness, the following adverse events are considered as adverse events of special interest and must be reported on AE page of the CRF.

In all patients:

- AEs leading to discontinuation study treatment
- Anaphylactic/anaphylactoid reactions

In patients treated with anakinra, the following AEs will be considered of special interest:

- Severe neutropenia defined as neutrophil count < 500/mm^3. No other AEs are required to be reported on the AE page of the CRF

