##### 3.2.1 Secondary endpoints supporting the secondary objective

- Total mortality rate (day 28)
- Mortality 48 hours, 7 days, in ICU and hospital
- Viral clearance / viral shedding
- Frequency and severity of AEs:
  - Treatment-emergent severe fatal and life-threatening serious adverse events (SAEs).
  - Adverse events leading to premature discontinuation of study treatment.
  - Anaphylactic/anaphylactoid reactions.

- 
- Anakinra treatment group: Severe neutropenia.
  - Treatment-emergent laboratory abnormalities.

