## 4.4 Treatments

### 4.4.1 Treatments administered

According to the randomization schedule, patients in arm A will receive (IMP) and standard of care and patients in arm B will receive standard of care only, see Table 1.

The treatment standard of care will be based on hydroxychloroquine and/or lopinavir-ritonavir and/or azithromycin.

Table 1:

| Arm | Investigational product | Dosage form | Route         | Daily dose                                                                                           | Dosage regimen              |
|-----|-------------------------|-------------|---------------|------------------------------------------------------------------------------------------------------|-----------------------------|
| A   | Anakinra                | Solution    | i.v. infusion | Days 1-15: 400 mg/day in total, divided into 4 doses given every 6 hours                             | 4 times daily for 15 days   |
| A   | Hydroxychloroquine      | Tablets     | Oral          | Day 1-15: 400 mg/day in total, divided into 2 doses given every 12 hours (loading dose: 400 mg/12 h) | 2 times daily for 5 days    |
| A   | Lopinavir-Ritonavir     | Tablets     | Oral          | Day 1-15: 800/200 mg/day in total, divided into 2 doses given every 12 h                             | 2 times daily for 5-7 days. |
| A   | Azithromycin            | Tablets     | Oral          | Day 1-15: 500 mg /day                                                                                | 1 time daily for 5 days.    |
| B   | Hydroxychloroquine      | Tablets     | Oral          | Day 1-15: 400 mg/day in total, divided into 2 doses given every 12 hours (loading dose: 400 mg/12 h) | 2 times daily for 5 days    |
| B   | Lopinavir-Ritonavir     | Tablets     | Oral          | Day 1-15: 800/200 mg/day in total, divided into 2 doses given every 12 hours                         | 2 times daily for 5-7 days. |
| B   | Azithromycin            | Tablets     | Oral          | Day 1-15: 500 mg /day                                                                                | 1 time daily for 5 days.    |

---

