##### Reporting of serious adverse events

All fatal and life-threatening SAEs occurring after study drug initiation and up to the end of study visit must be reported on AE pages in the CRF and on an SAE form, regardless of the investigator-attributed causal relationship with study treatment.

No other SAEs are required to be reported on AE page of the CRF and on the SAE form to Sobi drug safety department.

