#### 6.3.4.4 Adverse events

Reported AEs during the study will be coded using MedDRA. The incidence of AEs will be summarized in frequency tables by treatment, system organ class, preferred term and maximum severity. Separate tabulations will be performed for serious and non-serious AEs.

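### AE reporting rules conflict and differ by arm, so the non-serious AE table and the severe-neutropenia row would partly compare reporting duties

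*Protocol*

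**What the plan says.** Five parts of the protocol bear on this.

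- **Section 4.5.4.1 (Adverse events)** sets a full duty for one treatment: "All AEs for the patients that have received anakinra should be reported irrespective of causality to meet regulatory requirements". It has no corresponding sentence for patients on standard of care alone.
- **Section 4.5.4.3 (Reporting of adverse events)** gives a short list. For all patients it names AEs leading to discontinuation of study treatment and anaphylactic or anaphylactoid reactions. It then adds one item for one arm, severe neutropenia (neutrophils below 500/mm³), introduced by "In patients treated with anakinra, the following AEs will be considered of special interest". It closes with "No other AEs are required to be reported on the AE page of the CRF". Section 3.2.1 repeats the restriction at endpoint level: "Anakinra treatment group: Severe neutropenia".
- **Section 4.5.4.3 (Reporting of serious adverse events)** says: "All fatal and life-threatening SAEs occurring after study drug initiation and up to the end of study visit must be reported on AE pages". It adds: "No other SAEs are required to be reported on AE page of the CRF and on the SAE form to Sobi drug safety department".
- **Section 4.4.1** describes the arms: "patients in arm A will receive (IMP) and standard of care and patients in arm B will receive standard of care only".
- **Section 6.3.4.4** plans the output: "The incidence of AEs will be summarized in frequency tables by treatment, system organ class, preferred term and maximum severity", with separate tables for serious and non-serious events.

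In Table 3 the AE row is marked at Visits 1 to 4 (Day 1 to Day 15) and is empty at Visit 5 (Day 28).

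**The concern.** A by-treatment AE table can be read as a comparison only if an event of a given kind had the same chance of being written down in each arm. Here the full reporting duty in section 4.5.4.1 attaches to receipt of anakinra, and section 6.2 groups patients by treatment received for safety. The difference in duty therefore coincides with the columns of the table. The trial is open-label (section 4.4.6), so whoever completes the AE page knows which duty applies.

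A raised AE count under anakinra could then be real, or could come from sites reading section 4.5.4.1 for arm A and section 4.5.4.3 for arm B. The tables would not show which. Later analysis cannot repair this, because AEs that were never recorded cannot be recovered.

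**Working it through.** The protocol states no AE rate and no figure that depends on one, so there is nothing of its own to reproduce. The check compares the text and then adds an illustration on assumed rates.

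**1. Reporting duty by arm, as written**

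| Event type | Anakinra + standard of care | Standard of care only |
|---|---|---|
| Fatal or life-threatening SAE | required | required |
| AE leading to discontinuation | required | required |
| Anaphylactic/anaphylactoid reaction | required | required |
| Neutrophils <500/mm³, not covered by a row above | required (4.5.4.3) | not required |
| Any other AE | required by 4.5.4.1, not required by 4.5.4.3 | not required |

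The first three rows match. The fourth differs by arm under either section. The fifth differs by arm if section 4.5.4.1 is followed.

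**2. SAE scope.** Section 4.5.4.2 defines six seriousness criteria. Section 4.5.4.3 requires two (fatal, life-threatening), which leaves 6 − 2 = 4 not required unless the event also falls in another row of the table. This limit is the same in both arms. It makes the serious table incomplete but does not tilt it.

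**3. SAE window.** The start is study drug initiation. Arm B receives no anakinra, and section 4.4.2.1 uses the term study drug for the product the manufacturer supplies. Table 1, however, lists arm B's medicines in its investigational-product column, and section 4.5.1.3 places the first dose of study drug after randomisation to either group. Section 4.5.4.4 applies the same starting phrase to pregnancies whatever the treatment. Arm B's start is therefore unclear, but arm B is not excluded. The end is the end-of-study visit, whereas Table 3 prompts for AEs only to Day 15.

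**4. Illustration of differential recording.** Inputs:

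- From section 6.1: 90 per arm, and 90 × (1 − 0.10) = 81 after the stated 10% loss.
- Assumed: the same true AE rate p in both arms; arm A records all events; arm B records a share f.

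The apparent risk ratio is p/(p·f) = 1/f. The chance of a nominal two-sided p<0.05 is Φ[(d − 1.96·se₀)/se₁], where d = p − p·f, se₀ uses the pooled rate and se₁ the separate rates.

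For p = 0.30, f = 0.5, n = 81:

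- d = 0.15, pooled rate = 0.225
- se₀ = √(0.225 × 0.775 × 2/81) = 0.0656
- se₁ = √(0.30 × 0.70/81 + 0.15 × 0.85/81) = 0.0645
- (0.15 − 1.96 × 0.0656)/0.0645 = 0.33, and Φ(0.33) = 0.63

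| Share f recorded in arm B | Apparent risk ratio | p = 30%, n = 81 | p = 20–50%, n = 81 | p = 20–50%, n = 90 |
|---|---|---|---|---|
| 0.25 | 4.0 | 96% | 83–100% | 87–100% |
| 0.50 | 2.0 | 63% | 43–92% | 47–94% |
| 0.75 | 1.33 | 19% | 13–36% | 14–39% |

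With equal recording the figure would be about 5%.

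**5. Neutropenia row.** Assume the same true rate in both arms. Expected AE entries among 81 anakinra patients are 81 × 0.01 = 0.8, 81 × 0.02 = 1.6 or 81 × 0.05 = 4.1. In arm B an entry is required only if the event is fatal, life-threatening or leads to discontinuation. The data for an even comparison are already planned: section 4.5.3.6 schedules the differential count at Visits 1 to 4 without restriction by arm, and section 6.3.5 summarises it.

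**The case against.** The strongest defence is that limited safety collection was a deliberate choice for an approved drug in an emergency, and that section 4.5.4.3 collects the event types section 3.2.1 names. On that view section 4.5.4.1 concerns regulatory reporting, section 4.5.4.3 governs the CRF page, and a site that follows the explicit CRF instruction produces no general excess under anakinra. Section 6.3.4.4 also plans no test: it describes reported AEs, and section 6.3.1 makes secondary endpoints descriptive.

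Much of this stands. Selective collection is defensible, and the illustration uses assumed rates and a test nobody planned. What does not stand is the claim that the two sections separate cleanly. Section 4.5.4.1 sits in the safety assessments, is not confined to a route other than the CRF, and covers one treatment. Even if every site follows section 4.5.4.3, the neutropenia item still differs by arm. A descriptive table set out by treatment will also be read as a comparison.

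A reader might infer more than the protocol supports:

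- **That the SAE limit biases the comparison.** It applies to both arms. Four of six criteria are not required, but the protocol gives no share by number of events, and not required does not mean unrecorded.
- **That arm B has no SAE window.** Section 4.5.4.3 (Reporting procedures) requires fatal and life-threatening SAEs whichever treatment was received.
- **That arm B must show zero neutropenia.** Cases that are fatal, life-threatening or lead to discontinuation are reportable there.
- **That the main risk, serious infection, is missed.** Nothing in the protocol ranks infection as the main risk, and an infection that is fatal, life-threatening or leads to discontinuation is reportable.

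**Conclusion.** The point holds for specific parts of the safety reporting. Sections 4.5.4.1 and 4.5.4.3 contradict each other, the fuller duty names anakinra recipients only, and severe neutropenia is a listed AE and endpoint in one arm although section 6.3.4.4 tabulates by treatment. The parts affected are the non-serious AE table and the neutropenia row. It would go too far to say that no by-treatment safety table is fair: fatal and life-threatening SAEs, anaphylactic reactions and discontinuation AEs are required in all patients.

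The size depends on how sites resolve the contradiction. If all follow section 4.5.4.3, only neutropenia is affected. If section 4.5.4.1 is applied in arm A and section 4.5.4.3 in arm B, equal true risk could appear as a risk ratio of 1.33 to 4.0 for recorded shares of 75% down to 25%. Those shares and the AE rates are assumptions. The unclear start in arm B and the missing Day 28 prompt are smaller faults in the same text. The primary analysis is not touched. This should be corrected because collection, unlike analysis, cannot be redone.

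**What to change.** 1. Reconcile sections 4.5.4.1 and 4.5.4.3 into one reporting list that applies identically to both arms.
2. Start the AE/SAE window at randomisation in both arms, and add an AE/SAE entry at Visit 5 in Table 3 to match the end-of-study limit.
3. Tabulate neutrophils below 500/mm³ in both arms from the differential counts at Visits 1 to 4, with the number of patients who have a count at each visit. Drop the one-arm restriction in sections 3.2.1 and 4.5.4.3.
4. State in section 6.3.4.4 that the by-treatment tables cover only events captured under the same rule in both arms, and label the serious table as limited to the SAE types collected.

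The cost is small: wording and CRF edits, one added prompt at the Day 28 contact, and no new tests. Section 7.2 keeps scheduled laboratory results off the paper CRF, so the counts must come from laboratory records, which section 6.3.5 already needs. Widening collection to all SAEs is a separate trade-off and is not needed to resolve this point.

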#### 4.3.2 Exclusion criteria

The presence of any of the following will exclude a patient from inclusion in the study:

- Need for oro-tracheal intubation and/or invasive mechanical ventilation at the start of the study.
- AST/ALT with values greater than 5 times normal levels.
- Neutrophils < 1.500 cell/mmc.
- Platelets < 50.000 cell/mmc.
- Sepsis or pneumonia documented by other pathogens than SARS-CoV-2.
- Existence of any life-threatening comorbidity or any other medical condition that, in the investigator's opinion, makes the patient unsuitable for inclusion.
- Inability to obtain informed consent.
- Positivity for HBV or HCV.
- Patient with active tuberculosis (It is at the discretion of the researcher to perform the tuberculin test on the patient in the screening period if it is considered a risk population and on patients with active tuberculosis manifestations).
- Pregnancy.
- Use of other previous or concomitant biological treatments. Patients in concomitant treatment with other biologicals that may interfere will be excluded: tocilizumab, canakinumab, TNFalfa inhibitors, JAKinibs
- Severe renal dysfunction (estimated glomerular filtration rate  $\leq 30$  ml / min / 1.73 m^2) or receive continuous renal replacement therapy, hemodialysis or peritoneal dialysis.
- Uncontrolled hypertension (sitting systolic blood pressure > 180 mmHg or diastolic blood pressure > 110 mmHg).
- Administration of plasma from convalescent patients who have recovered from SARS-CoV-2 infection.
- History of hypersensitivity or allergy to any component of the study drug.
- Enrollment in another concurrent intervention clinical trial, or intake of an investigational medication within three months or 5 half-lives prior to inclusion in this study, if deemed to interfere with the objectives of this study as assessed by the investigator.

- Predictable inability to cooperate with given instructions or study procedures.

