#### 4.4.7 Concomitant therapy

##### 4.4.7.1 *Background therapy*

A course of 1 pulse of IV methylprednisolone for 3 consecutive days (pulse dose recommended 250-500 mg) should be considered under investigators clinical criteria in both arms at any time during the study.

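### Non-severe secondary infections need not be recorded under 4.5.4.3, while 4.5.4.1 asks for every adverse event under anakinra, so infection cannot be compared without bias between arms

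*Protocol*

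**What the plan says.** Section 4.5.4.3 (Reporting of adverse events) lists the events that must go on the adverse-event page whether or not they are serious:

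- In all patients: "AEs leading to discontinuation study treatment" and "Anaphylactic/anaphylactoid reactions".
- In anakinra patients only: severe neutropenia.

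It then closes the list: "No other AEs are required to be reported on the AE page of the CRF".

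The next subsection (Reporting of serious adverse events) starts with "All fatal and life-threatening SAEs occurring after study drug initiation and up to the end of study visit must be reported", regardless of causality, and closes that list too: "No other SAEs are required to be reported on AE page of the CRF and on the SAE form".

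Other sections bear on the same point:

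- **4.5.4.1** asks that every adverse event in patients who received anakinra be reported, whatever its cause.
- **4.5.4.2** counts prolongation of an existing hospital stay as a criterion for seriousness.
- **3.2.1** has no infection endpoint among the safety endpoints.
- **Table 3** schedules adverse events at Visits 1 to 4 but not at Day 28.
- **6.3.4.4** plans MedDRA-coded tables by system organ class, preferred term and maximum severity, with serious and non-serious events shown separately.
- **4.1** gives both efficacy and safety as the purpose of the trial.

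**The concern.** A safety comparison is only as good as the rule that decides what is written down. Infection appears on neither closed list, and 4.5.4.1 points the other way for one arm only.

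Infection is relevant to this population on the protocol's own terms. Section 4.3.2 excludes "Sepsis or pneumonia documented by other pathogens than SARS-CoV-2", active tuberculosis, HBV or HCV positivity, and low neutrophils. Severe neutropenia is an event of special interest under anakinra. Methylprednisolone pulses "should be considered under investigators clinical criteria in both arms at any time during the study" (4.4.7.1).

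Two outcomes are at stake. If sites follow the closed list in both arms, the tables in 6.3.4.4 could show few infections partly because most were never requested. If sites follow 4.5.4.1 for anakinra and 4.5.4.3 for control, the tables could show an excess under anakinra that comes from recording alone. An analysis plan cannot repair either, because events that never reach the CRF cannot be restored. The result matters beyond the trial: section 2.3 says positive results could help define standard treatment, and 6.1 foresees use for regulatory approval.

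**Working it through.** **Step 1: set the rules side by side.** The protocol states no figure on this point, so there is none to reproduce. The table shows what each rule requires for a secondary infection.

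| Infection | 4.5.4.3, both arms | 4.5.4.1, anakinra patients |
|---|---|---|
| Fatal or life-threatening | recorded | recorded |
| Leads to stopping study treatment | recorded | recorded |
| Prolongs hospital stay (serious under 4.5.4.2), none of the above | not required | recorded |
| Other treated infection | not required | recorded |

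The conflict lies in the last two rows. The second row may also work unevenly, because arm B has no anakinra to stop.

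**Step 2: check whether other data recover the missing rows.** They do so only indirectly.

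- White cells and CRP are measured at Visits 1 to 4 (Table 4) and temperature at the same visits (4.5.4.7). Section 2.1 says anakinra lowers acute-phase reactants, so CRP is affected by the drug under test.
- Antibiotic use is a weak proxy. Azithromycin may be part of standard care in both arms (4.4.1), antimicrobials are unrestricted, and only concomitant therapy that the investigator regards as relevant is recorded (4.4.7.2).
- The repeat chest film is at Day 15 and is reported as normal or abnormal (4.5.3.5), in patients who all entered with infiltrates.
- The committee in 4.5.4.11 can review only what is recorded.

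**Step 3: illustrate the size.** Inputs: n = 90 per arm (6.1), two-sided α = 0.05. The infection rates and capture fractions f are assumptions; the protocol gives neither. With recorded rates p₁ and p₂, d = |p₁ − p₂| and p̄ = (p₁ + p₂)/2:

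- SE₀ = √[2p̄(1 − p̄)/n]
- SE₁ = √[p₁(1 − p₁)/n + p₂(1 − p₂)/n]
- probability of significance ≈ Φ[(d − 1.96·SE₀)/SE₁]

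*(a) Closed list followed in both arms.* Assume true rates of 10% (control) and 20% (anakinra).

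- All recorded: 90 × 0.10 = 9 against 90 × 0.20 = 18. SE₀ = 0.0532, SE₁ = 0.0527, and Φ[(0.10 − 0.1043)/0.0527] = 0.47.
- f = 0.5: 4.5 against 9, power 0.25.
- f = 0.2: 1.8 against 3.6, power 0.12.

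Other assumed pairs behave alike:

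| Assumed true rates (control, anakinra) | All recorded | f = 0.5 | f = 0.2 |
|---|---|---|---|
| 5%, 10% | 0.25 | 0.14 | 0.08 |
| 10%, 20% | 0.47 | 0.25 | 0.12 |
| 15%, 30% | 0.68 | 0.36 | 0.16 |

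*(b) Everything recorded under anakinra, closed list in control.* Assume the same true rate of 10% in both arms, so that there is no real difference.

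- f = 0.5 in control: 9 (anakinra) against 4.5 recorded. The recorded rates are 0.10 and 0.05, and the probability of a significant difference is 0.25.
- f = 0.2 in control: 9 against 1.8. The recorded rates are 0.10 and 0.02, SE₀ = 0.0354, SE₁ = 0.0349, and Φ[(0.08 − 0.0694)/0.0349] = 0.62.

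An unbiased comparison would have about 0.05 in case (b). The normal approximation is rough at such small counts, so the figures show direction and order of size only.

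**The case against.** The case against is substantial, and much of it limits the point.

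- **The plan does capture the worst infections.** Fatal, life-threatening and treatment-stopping infections are reportable, coded and tabulated. This stands. A reader might infer that the trial cannot show infection harm at all; the text does not support that. What is lost is the remainder, including infections that only prolong the stay.
- **Section 4.5.4.1 asks for all events under anakinra.** This stands too, so it would be wrong to say without qualification that infections go unrecorded in both arms. But it sharpens the problem, because the fuller rule covers one arm only.
- **Infection as the most foreseeable harm.** A reader might infer this from the exclusions and the steroid pulses. The protocol does not say it. It names injection-site reactions as the commonest events (4.5.4.1), reports no safety concerns from the intravenous studies (4.4.4.1), and does not call anakinra an immunosuppressant. Excluding pneumonia from other pathogens may simply serve to define COVID-19 pneumonia.
- **Blurring of the primary endpoint.** A reader might also infer that a superinfection leading to ventilation could not be told apart from COVID-19 progression. Such an infection would usually meet the life-threatening criterion and reach an SAE form with a causality assessment, so this is not a strong argument.
- **Short event lists suit an emergency trial on paper CRFs.** This is fair as a general choice. It does not justify two rules that disagree, or tables of non-serious events that the closed list leaves largely unfilled.
- **Power is modest even with full recording.** This is true: 0.47 for an assumed doubling from 10%. The gain is mainly an unbiased estimate with a confidence interval.

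**Conclusion.** The point holds in a limited form. Sections 4.5.4.1, 4.5.4.3 and 6.3.4.4 disagree on which adverse events are collected. Under 4.5.4.3 alone, an infection that is not fatal, not life-threatening and does not stop treatment is not required on the CRF in either arm, even when 4.5.4.2 would class it as serious. If 4.5.4.1 is followed for anakinra patients, recording is unequal. Neither reading gives an unbiased comparison of infection between arms, so that part of the safety aim in 4.1 is not met.

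The textual conflict needs no assumption. Its size does: the counts and probabilities above rest on assumed infection rates and capture fractions and are illustrations only. The change is well worth making because it is cheap and the missing data cannot be recovered later.

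**What to change.** 1. Reconcile 4.5.4.1, both reporting subsections of 4.5.4.3, and 6.3.4.4 into one recording rule, applied identically to both arms.
2. Add to the all-patients list in 4.5.4.3: *new bacterial, fungal or mycobacterial infection, or viral reactivation, requiring treatment*. Record it as diagnosed in routine care, from randomisation to the Day 28 contact.
3. Tick the adverse-event row of Table 3 at Day 28. This also brings the table into line with the SAE rule, which already runs to the end-of-study visit.
4. In 6.3.4.4, report the incidence of these infections by arm with a risk difference and 95% CI.

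This changes recording only; it adds no test and alters no treatment. The cost is a short amendment, an added line on the CRF, one table and some extra transcription at sites. Two limits remain. Day 28 may be a telephone call, so detail on late infections will be thin. And because the trial is open-label, infections may be looked for or diagnosed differently by arm; a common rule reduces that risk but does not remove it.
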